### Reassessments

2.6

Participants undergo reassessment of the primary and secondary outcomes (Table 2) after the 6-week intervention and 6 months following completion of interventions (Fig. 2). Similar to the baseline assessment, participants are emailed a link to complete the assessment questionnaires and mailed the actigraph with a postage-paid envelope to return the actigraph.

**Table 2 tbl2:** Primary and secondary outcomes.

Sleep Outcomes: (Aim 1)
1. Insomnia Severity Index (ISI) [35] (primary outcome)
2. Pittsburgh Sleep Quality Index (PSQI) [44]
3. Actigraphy
Fatigue and Quality of Life Outcomes: (Aim 2)
1. Modified Fatigue Impact Scale (MFIS) [45]
2. Fatigue Severity Scale (FSS) [46]
3. Multiple Sclerosis Impact Scale (MSIS-29) [47]
Secondary Outcomes: (Exploratory Aim 3)
1. Patient-Determined Disability Steps (PDDS) [32]
2. Patient Health Questionnaire (PHQ-9) [41] to assess depression
3. Generalized Anxiety Disorder Assessment (GAD-7) [49]
4. Sleep Self-Efficacy Scale (SESS) [50]
5. Adherence to CBT-I protocol (*Gathered from sleep log*: number of days/week got out of bed at agreed upon time, number of times got out of bed if unable to sleep within 20 min, number of nights/week conducted wind-down routine; a percentage will be calculated)

**Fig. 2 fig2:**
[figure not shown]
Overview of study protocol by assessments time points.

### Study arms

2.7

#### Cognitive behavioral therapy for insomnia (CBT-I)

2.7.1

The CBT-I program is a 1x/week, 6-week one-on-one program via video conferencing (HIPAA-compliant Zoom). The program is based on standard CBT-I manuals [51,52]. Participants maintain a sleep diary during the program to aid in tailoring the program. Each session includes a summary and graphing of sleep diary data, an assessment of treatment gains and adherence, and determination if upward titration of total sleep time is warranted. The general session outlines are as follows with each session lasting 45–60 min:

*Session 1*: subjective sleep history and description of current sleep issues, education regarding physiological mechanisms of sleep using the two process of model of sleep [53] and 3P model of insomnia [54], and tailored sleep promotion techniques, collaboratively set time in bed restriction, discuss strategies for stimulus control (if fall risk, perform counter-control in bed instead), discuss avoiding/limiting naps (limit napping to ≤ 30 min, to take the nap as early in the day as possible, and delaying bedtime to a later time may be necessary until they were adequately tired).

*Session 2*: review sleep promotion techniques, introduce diaphragmatic breathing and deep breathing as relaxation techniques to reduce pre-sleep arousal.

*Session 3*: introduce mindfulness as a technique to reduce pre-sleep arousal.

*Session 4*: introduce progressive muscle relaxation (PMR) as relaxation technique to reduce pre-sleep arousal (if concern about contraction portion of PMR may increase symptoms or spasticity, recommend only performing relaxation strategies).

*Session 5*: cognitive restructuring for negative sleep beliefs as needed, reinforce and/or continue to tailor various techniques.

*Session 6*: discuss relapse prevention and maintenance of sleep gains.

#### Active control group (control)

2.7.2

The control group matches the intervention group for time, contact with research personnel, and delivery method. The control group receives basic sleep hygiene and lifestyle education which is very commonly used as the control for CBT-I. Importantly, participants in the control condition do not receive active components of CBT-I (i.e. time in bed restriction, stimulus control, cognitive restructuring, relaxation strategies, psychoeducation) or strategies to change sleep behavior (i.e. motivational interviewing, goal setting for sleep). The control program is a 1x/week, 6-week one-on-one program via video conferencing (HIPAA-compliant Zoom). The general session outlines are as follows with each session lasting 45–60 min and includes starting the session with basic stretches and ending the session with same stretches:

Session 1: education on sleep stages.

Session 2: education on sleep hygiene (focus on environment of temperature, noise, light, optimal sleeping positions).

Session 3: education on sleep hygiene (focus on stimulants/depressants of caffeine, medications, nicotine, alcohol, screen time).

Session 4: education on sleep hygiene (focus on diet/nutrition of large/spicy meals, fluid intake, basic diet recommendations).

Session 5: education on sleep hygiene (focus on exercise).

Session 6: discuss remaining questions.

## Statistical plan and data analysis

3

### Sample size justification

3.1

We will enroll 70 participants (35 in each of the two groups) in our study. Our sample size calculations are guided by effect size estimates for the primary outcome of ISI and PSQI from our pilot studies [28,29]. We hypothesize that CBT-I will perform better than the Control group for ISI and PSQI. Our hypotheses are – $H_{0}:\mu_{CBT-I}\leq \mu_{Control}$ vs $H_{0}:\mu_{CBT-I}>\mu_{Control}$ where the μ represents the mean scores of the two arms at 6 week and 6 month assessment after adjusting for the baseline.

Our calculations are purposely done in a conservative way considering the following two limitations of our pilot study comparing CBT-I to an Active Control and to a brief education group (BE) – {i} Our preliminary study was a pilot study with only 10 subjects in the CBT-I, Active Control and BE arms, and {ii} There was no significant difference in the Active Control vs BE arm for both the primary and secondary outcomes in our pilot study. Thus, we have made the following assumptions in the power analysis calculations for the proposed study – {i} The higher of the mean change scores of the Active Control and BE arm in the pilot study is considered as $\mu_{Control}$, {ii} The mean change score for CBT-I in the pilot study is considered as $\mu_{CBT-I}$, {iii} The higher of the two standard deviations (of effect size) for the CBT-I and Control group is used as the common standard deviation, {iv} sample size calculations are done with a two-sided test, with type I error set at 5 % and target power is taken as 90 %.

A ‘*Repeated Measures design’* with autocorrelation of ρ=0.5 (between the 6 week and 6 month assessment) and a type I error of 5 % was used to conduct the sample size calculations. With the assumptions mentioned above, for the *primary outcome of ISI*, a sample size of 17 in each of the two arms (n = 34 total) is required to detect a $\mu_{CBT-I}$ value of 13.8 versus $\mu_{Control}$ value of 8.1 (with common standard deviation σ=5.8) with 90 % power. Analogously, in the case of *primary outcome of PSQI*, a sample size of 25 in each of the two arms (n = 50 is required to detect a $\mu_{CBT-I}$ value of 6.7 versus $\mu_{Control}$ value of 4.6 (with common standard deviation σ=2.6) with 90 % power. Thus, max (34, 50) = 50 is chosen. The attrition rate from our prior preliminary efficacy trials of CBT-I in people with MS were: 16.7 % in-person CBT-I [28], 9.1 % in brief education [28], and 0 % in tele-health delivered CBT-I [29]. To be cautious, we will anticipate an attrition rate of 25 % due to the delayed reassessment, and so 50/0.75 ≈ 67 (rounded up to 68) is chosen. Looking at overall capability at enrolling participants, we have decided to enroll a total of 70 subjects in our study. We used the *‘Test for Two Means in a Repeated Measures Design’* platform in PASS 2020 to conduct our sample size calculations.

### Statistical Plan

3.2

We will conduct an intention-to-treat analysis for each outcome as well as for those who complete the delayed reassessment. Descriptive statistics will be reported using mean and standard deviation for continuous variables and with frequency counts for categorical variables. The study biostatistician will not be aware of group allocation and will use the SAS statistical software to run all analyses.

#### Aim 1: To determine if CBT-I in individuals with MS will improve insomnia symptoms and sleep quality

3.2.1

*Hypotheses*: CBT-I will improve insomnia symptoms (primary outcome; measured using the Insomnia Severity Index) and sleep quality (measured using the Pittsburgh Sleep Quality Index) and will increase sleep efficiency and total sleep time (measured by actigraphy) compared to active control after intervention and after 6 months.

*Statistical Plan*: A repeated measures model (RMM) with two groups will be used to analyze the primary outcome of ISI and secondary outcome of PSQI at 6 weeks and 6 months. The analysis will be done adjusting for baseline as a covariate. With only two time points, the analysis is simplified (compound symmetry structure) and will be conducted using a type I error of 5 %. If there is a significant between group difference, we will use the pairwise comparison from the RMM to compare the two groups at 6-weeks and at 6 months. Point estimates of the mean scores for the two groups at all time points will be reported along with the corresponding 95 % confidence interval and p-values.

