#### Aim 2: To determine if CBT-I in individuals with MS will improve the MS symptom of fatigue

3.2.2

*Hypotheses*: CBT-I will improve fatigue (measured using Fatigue Severity Scale and Modified Fatigue Impact Scale) and health-related quality of life (measured by the Multiple Sclerosis Impact Scale) compared to active control after intervention and after 6 months.

*Statistical Plan*: The same statistical analysis plan used for Aim 1 will be used in Aim 2. A RMM with two groups will be used to analyze the secondary outcomes of MFIS, FSS and MSIS. The analysis will be done adjusting for baseline as a covariate. With only two time points, the analysis is simplified (compound symmetry structure) and will be conducted using a type I error of 5 %. If there is a significant between group difference, we will use the pairwise comparison from the RMM to compare the two groups at 6-weeks and at 6 months. Point estimates of the mean scores for the two groups at all time points will be reported along with the corresponding 95 % confidence interval and p-values.

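### Compound symmetry is fixed because there are two visits, yet two visits need no imposed structure; per-visit intervals may be mis-sized if the 6-week and 6-month variances differ

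*Protocol article*

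**What the plan says.** Section 3.2.1 (Aim 1) uses a repeated measures model with two groups to "analyze the primary outcome of ISI and secondary outcome of PSQI at 6 weeks and 6 months". On baseline it says: "The analysis will be done adjusting for baseline as a covariate". It then fixes the covariance and gives its only reason in the same sentence: "With only two time points, the analysis is simplified (compound symmetry structure". The type I error is set at 5%. No unstructured or heterogeneous alternative, fallback or robust standard error is named.

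The same model supplies the visit-level results. If the overall group difference is significant, "we will use the pairwise comparison from the RMM to compare the two groups at 6-weeks and at 6 months". Reporting is also by visit: "Point estimates of the mean scores for the two groups at all time points will be reported along with the corresponding 95 % confidence interval", together with p-values.

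Section 3.2.2 (Aim 2) carries this over to MFIS, FSS and MSIS: "The same statistical analysis plan used for Aim 1 will be used in Aim 2". It repeats the covariance sentence.

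Section 3.1 plans with one SD per outcome (ISI 5.8, PSQI 2.6) and a correlation of 0.5 between the two follow-up visits. On losses it says "we will anticipate an attrition rate of" 25%, because of the delayed reassessment.

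**The concern.** A 2×2 covariance matrix has three parameters: a variance at each visit and one covariance. Compound symmetry keeps two of them by setting the variances equal. Having only two visits settles the form of the correlation, since there is just one, but it says nothing about whether the variances are equal. It is also the case in which leaving the matrix free costs least.

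The hypotheses for both aims concern the effect after the intervention and after 6 months, so the visit-level estimates matter. Under compound symmetry their standard errors come from one pooled variance. If the true variances differ, a pooled SD is too large for one visit and too small for the other. The same would hold for each outcome analysed this way.

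The relevant variances are residual, after baseline adjustment. They can differ even when the raw SDs are equal, if baseline predicts the 6-week score better than the 6-month score.

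**Working it through.** **1. The plan's own figures.** Inputs from section 3.1: two-sided 5%, 90% power, ρ = 0.5. The effective SD for the mean of two visits is σ√((1+ρ)/2) = σ√0.75.
- ISI: difference 13.8 − 8.1 = 5.7; effective SD 5.8 × 0.866 = 5.02. This gives 17 per arm (power 91.1%), as stated.
- PSQI: difference 6.7 − 4.6 = 2.1; effective SD 2.6 × 0.866 = 2.25. This gives 25 per arm (power 90.9%), as stated.
- Attrition: 50/0.75 = 67, as stated.

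The sample size reproduces, and the covariance choice does not change it.

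**2. Interval width under compound symmetry, complete data.** Let r be the 6-month to 6-week residual SD ratio. The pooled variance is (1 + r²)/2 in units of the 6-week variance. Used width divided by correct width is √((1+r²)/2) at 6 weeks and √((1+r²)/2)/r at 6 months. Coverage is 2Φ(1.96 × width ratio) − 1. The article gives no value of r, so a range is shown.

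| r (assumed) | 6-week width ratio | coverage | 6-month width ratio | coverage |
|---|---|---|---|---|
| 0.8 | 0.91 | 92.4% | 1.13 | 97.3% |
| 1.0 | 1.00 | 95.0% | 1.00 | 95.0% |
| 1.1 | 1.05 | 96.1% | 0.96 | 93.9% |
| 1.2 | 1.10 | 97.0% | 0.92 | 92.9% |
| 1.3 | 1.16 | 97.7% | 0.89 | 92.0% |
| 1.5 | 1.27 | 98.8% | 0.85 | 90.4% |

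Worked example, r = 1.3: (1 + 1.69)/2 = 1.345; √1.345 = 1.16; 1.16/1.3 = 0.89.

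**3. How r could depart from 1.** With equal raw SDs, r = √((1 − c₂²)/(1 − c₁²)), where c₁ and c₂ are the correlations of baseline with the 6-week and 6-month scores. Assumed values of 0.5 and 0.3 give √(0.91/0.75) = 1.10. Values of 0.7 and 0.3 give √(0.91/0.51) = 1.34.

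**4. Simulation check.** REML fits of both structures were compared with 35 per arm, ρ = 0.5, r of 1, 1.1, 1.3 and 1.5, and 0% or 25% missing at random at 6 months. There were 800 runs per cell (Monte Carlo error about 0.8 points).
- At r = 1.3 with 25% missing, 6-month coverage was 91.0% under compound symmetry and 95.2% under unstructured.
- Unstructured coverage lay between 94% and 97% at both visits in every cell.
- At r = 1, unstructured intervals were wider by about 0.4% to 1.5%.
- The type I error of the overall test was identical under both structures with complete data. With 25% missing it was 0.041–0.061 under compound symmetry and 0.038–0.061 under unstructured.

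**5. The per-visit tests with the plan's gate.** Assumed SDs of 5.0 and 6.5 pool to √((25 + 42.25)/2) = 5.80. Taken alone, the visit tests would then have type I error of 2.3% at 6 weeks and 8.0% at 6 months. The plan runs them only after a significant overall difference, so the gated procedure was simulated (overall test taken as the mean of the two visits, an assumption; complete data; normal approximation; 35 per arm). The 6-month false-positive rates were:

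| SDs (assumed) | true effect | compound symmetry | unstructured |
|---|---|---|---|
| 5.0 / 6.5 | none | 3.7% | 3.0% |
| 5.0 / 6.5 | 5.7 points at 6 weeks only | 4.0% | 2.5% |
| 5.4 / 6.2 | none | 3.3% | 2.8% |
| 5.4 / 6.2 | 5.7 points at 6 weeks only | 3.3% | 2.5% |

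**The case against.** The strongest reply is that the harm is hypothetical. The article gives one SD per outcome and nothing by visit, and with equal residual variances compound symmetry is correct. At a ratio of 1.1 the error is about one coverage point. The overall test, which gates the visit comparisons, is essentially untouched, and so is the power calculation. All of this stands, and it sets the size of the point. It does not rescue the stated reason: a common planning SD is no evidence that the visits share a variance, and two visits do not make it so.

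A reader might infer three stronger claims that the document does not support.
- *The intervals will be wrong.* That requires unequal residual variances, which the article neither states nor rules out.
- *Certainty about durability will be overstated.* That requires the larger variance at 6 months. Relapse in some participants makes this conceivable, but at a ratio of 0.8 the 6-month interval is 13% too wide instead.
- *The 6-month test runs at about 8%.* That figure ignores the gate. The rate would approach 8% only if the overall test were almost always significant while the 6-month effect was zero.

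The gate does not repair the intervals, because they are reported at all time points. Degrees-of-freedom methods and the full list of fixed effects are details that an article may leave to the analysis plan, so their absence is not criticised here.

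**Conclusion.** The point holds as a minor one. Sections 3.2.1 and 3.2.2 impose an equal-variance assumption for a reason that does not support it. The possible consequence is confined to the per-visit intervals and comparisons. For assumed SD ratios from 1.1 to 1.3 the 6-week interval is 5% to 16% too wide and the 6-month interval 4% to 11% too narrow. The direction reverses below 1, and there is no error at 1. These figures rest on assumed ratios, since the article gives no visit-specific SD. The overall between-group conclusion and the sample of 70 do not depend on this choice in any material way.

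**What to change.** In sections 3.2.1 and 3.2.2, replace the compound symmetry specification with an unstructured covariance for the two follow-up visits, and drop the number of time points as the reason for a simplified structure. Nothing else in the analysis or the sample size needs to change.

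The cost is one more variance parameter, a one-option change in SAS, and intervals about 0.4% to 1.5% wider if the variances turn out to be equal. The change should be recorded before unblinded data are seen.

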#### Aim 2: To determine if CBT-I in individuals with MS will improve the MS symptom of fatigue

3.2.2

*Hypotheses*: CBT-I will improve fatigue (measured using Fatigue Severity Scale and Modified Fatigue Impact Scale) and health-related quality of life (measured by the Multiple Sclerosis Impact Scale) compared to active control after intervention and after 6 months.

*Statistical Plan*: The same statistical analysis plan used for Aim 1 will be used in Aim 2. A RMM with two groups will be used to analyze the secondary outcomes of MFIS, FSS and MSIS. The analysis will be done adjusting for baseline as a covariate. With only two time points, the analysis is simplified (compound symmetry structure) and will be conducted using a type I error of 5 %. If there is a significant between group difference, we will use the pairwise comparison from the RMM to compare the two groups at 6-weeks and at 6 months. Point estimates of the mean scores for the two groups at all time points will be reported along with the corresponding 95 % confidence interval and p-values.

#### Exploratory Aim 3: To explore the baseline characteristics of participants that predict improvement in sleep outcomes

3.2.3

HypothesisBaseline disability level, anxiety, depression, and sleep self-efficacy will predict responders and non-responders (i.e. higher disability, anxiety, and depression, lower sleep self-efficacy, and lower intervention adherence will predict non-responders; lower disability, anxiety, and depression, and higher sleep self-efficacy and level of intervention adherence will predict responders).

*Statistical Plan*: For Aim 3, the outcome is dichotomous (responders vs non-responders) and a logistic regression analysis will be conducted modeling responder status (defined as meeting the minimal clinically important difference of ≥ 6 points on the ISI) at 6 weeks. This will allow assessment of the effect of baseline predictors such as disability level, anxiety, depression, sleep self-efficacy level, and intervention adherence. The analysis will be conducted at the 5 % level of significance.

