While CBT-I is a first-line recommended behavioral intervention for insomnia according to guidelines from the American College of Physicians [25], the European Sleep Research Society [26], and the American Academy of Sleep Medicine [27], there are limited studies that have examined the effect of CBT-I on sleep outcomes and comorbid MS symptoms. We recently completed the first pilot randomized controlled trials to assess feasibility and preliminary efficacy of CBT-I modified specifically for pwMS [28,29]. Modifications that we made to the standard CBT-I program include: 1. For individuals who felt a nap was necessary for their health and wellbeing, the recommendation to avoid naps was modified to limit napping to ≤30 min, to take the nap as early in the day as possible, and delaying bedtime to a later time may be necessary until they were adequately tired; 2. For individuals with functional or mobility limitations or those who had concerns about falls (either individual or CBT-I provider), stimulus control was modified to perform a relaxation or distraction technique in bed; 3. For individuals who were concerned that the contraction portion of progressive muscle relaxation (PMR) might exacerbate spasticity (despite the standard instruction to gently tense muscle groups without causing discomfort), PMR was modified to focus solely on the relaxation component (i.e., releasing tension) without performing the contraction phase.

Whereas our pilot studies demonstrate feasibility and a large effect on sleep outcomes in pwMS following CBT-I [28,29], a well-designed adequately powered prospective randomized control trial (RCT) is needed to assess the efficacy of CBT-I delivered via telehealth compared to an appropriate control group to improve sleep outcomes (Aim 1) and fatigue and health-related quality of life (Aim 2). Also, determining the participant characteristics that predict improvement in sleep outcomes (Exploratory Aim 3) would help guide health care providers and individuals with MS to select an appropriate sleep intervention at an individual level.

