*Secondary Outcomes:* To explore the characteristics of participants that predict improvement in sleep outcomes (Exploratory Aim 3), disability (assessed by the Patient-Determined Disability Steps; PDDS) [32], depression (assessed by the Patient Health Questionnaire; PHQ-9) [41], anxiety (assessed by the Generalized Anxiety Disorder Assessment; GAD-7) [49], sleep self-efficacy (assessed by the Sleep Self-Efficacy Scale; SESS) [50], and adherence to the intervention are also assessed. Disability level, depression, anxiety, and sleep self-efficacy have a known bidirectional relationship with sleep and fatigue and are plausible predictors of responders and non-responders to CBT-I.1.Patient-Determined Disability Steps (PDDS) [32] scale is used to assess disability. It consists of a 9-point scale ranging from “normal” (score of 0) to “bedridden” (score of 8). The PDDS has been validated and highly associated with the Expanded Disability Status Scale [33].2.Patient Health Questionnaire (PHQ-9) [41] is a valid and reliable method to assess depression during the past 2 weeks. It consists of 9 items with a score ranging from 0 to 27. A tenth question that is not included in the summary score assesses how depressive symptoms affect functional level. The PHQ-9 is used as a screening tool and an outcome measure.3.Generalized Anxiety Disorder Assessment (GAD-7) [49] is a valid and reliable method to assess anxiety over the past 2 weeks. This questionnaire consists of 7 items, and the score from each item is summed for an overall score ranging from 0 to 21 with a higher score indicating a higher level of anxiety. An additional eighth question assesses if anxiety impacts daily activities and sociability.4.Sleep Self-Efficacy Scale (SESS) [50] is a 9-item self-report questionnaire used to measure sleep self-efficacy. The respondents indicate confidence in ability to accomplish 9 sleep behaviors on a 5-point Likert scale with 1 = “not confident” at all to 5 = “very confident”. The score ranges from 0 to 45 with a higher score indicating greater sleep self-efficacy.5.Adherence to CBT-I intervention: To assess adherence to the CBT-I intervention, the sleep log is used to assess number of mornings per week the participant got out of bed at agreed upon time, number of times got out of bed if unable to sleep within 20 min, and number of nights per week the participant conducted wind-down routine. A total percentage will be calculated and used as the outcome of interest.

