## Discussion

4

Insomnia is a common problem in people with MS [4], which often remains unrecognized and therefore untreated [5]. CBT-I has been shown to be highly effective in addressing sleep disturbances in people with primary insomnia [19,20], as well as in populations of people with insomnia comorbid with a variety of chronic conditions [18]. However, evidence on the efficacy of CBT-I for pwMS remains limited. Our previous pilot studies demonstrated feasibility and large improvements in sleep outcomes in pwMS following CBT-I [28,29]. The proposed study represents the next needed step to determine the efficacy of CBT-I in this population. Specifically, we will conduct an adequately powered prospective randomized control trial (RCT) to assess the efficacy of CBT-I delivered via telehealth compared to an appropriate control group to improve sleep outcomes (Aim 1) and fatigue and health-related quality of life (Aim 2). An Exploratory Aim 3 will determine the participant characteristics that predict improvement in sleep outcomes. This will help guide health care providers and individuals with MS to select an appropriate sleep intervention at an individual level. Addressing insomnia symptoms using CBT-I could represent a low-cost, low-risk, non-pharmacological option for improving sleep quality, fatigue, and quality of life in individuals with MS and could result in reduced disability, improved quality of life, increased employment, and reduced costs associated with care and support for individuals with MS.

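### The Exploratory Aim 3 model can show who improves but not who gains more from CBT-I than from control, so it does not support the stated use in choosing an intervention for an individual

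*Protocol article*

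**What the plan says.** All references are to the protocol article.

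- **Model (section 3.2.3).** "the outcome is dichotomous (responders vs non-responders) and a logistic regression analysis will be conducted modeling responder status" at 6 weeks. Response is "defined as meeting the minimal clinically important difference of ≥ 6 points on the ISI".
- **Predictors (section 3.2.3).** The model is to assess "baseline predictors such as disability level, anxiety, depression, sleep self-efficacy level, and intervention adherence". Randomised arm is not named, nor is any product of arm with a predictor. The test level is fixed: "The analysis will be conducted at the 5 % level of significance".
- **Analysis set.** Section 3.2.3 does not say whether both arms or only the CBT-I arm enter. Section 2.5 says the characteristics "are plausible predictors of responders and non-responders to CBT-I" and defines adherence for the CBT-I programme only. Section 2.7.2 says that controls do not receive the active CBT-I components.
- **Hypothesis (section 3.2.3).** Certain characteristics predict responders and non-responders. Aims 1 and 2 state a comparison with active control; Aim 3 does not.
- **Stated use.** The Introduction says that knowing the predictors "would help guide health care providers and individuals with MS to select an appropriate sleep intervention at an individual level". The Discussion repeats it: "This will help guide health care providers and individuals with MS to select an appropriate sleep intervention at an individual level".

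**The concern.** Choosing between interventions for a person requires knowing whether the difference between CBT-I and control varies with that person's characteristics. That is effect modification, and in a two-arm trial it is estimated by an arm-by-predictor interaction. A model of response on characteristics alone estimates prognosis: who improves, whatever the reason.

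The two can diverge in both directions. A factor that predicts improvement equally in both arms would look like a marker of suitability for CBT-I although the benefit over control is the same at every level. A factor that truly changes the benefit may show little or no main effect. At stake is the practical message of Aim 3: people might be steered towards or away from CBT-I on prognostic grounds alone, although the randomised control arm needed for the right comparison is available.

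**Working it through.** **Inputs.** Section 3.1 gives mean ISI change 13.8 (CBT-I) and 8.1 (control), common SD 5.8, correlation 0.5, two-sided 5% level, 90% power, 35 per arm and 25% attrition. Section 3.2.3 gives the 6-point threshold. No power or sample size is stated for Aim 3.

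**The plan's own figure.** For two follow-up visits, n per arm = 2 × (1.960 + 1.282)² × SD² × (1 + 0.5)/2 ÷ difference².

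- ISI: 2 × 10.51 × 33.64 × 0.75 ÷ 5.7² = 16.3, so 17, as stated.
- PSQI: 2 × 10.51 × 6.76 × 0.75 ÷ 2.1² = 24.2, so 25, as stated.

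The ISI inputs are therefore being read as the plan uses them.

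**Implied responder rates (normal change scores assumed).**

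- CBT-I: Φ((13.8 − 6)/5.8) = Φ(1.345) = 0.911
- Control: Φ((8.1 − 6)/5.8) = Φ(0.362) = 0.641
- Odds ratio for arm: (0.911/0.089) ÷ (0.641/0.359) ≈ 5.7

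**Reading 1: both arms pooled.** Responders are 35 × 0.911 = 31.9 and 35 × 0.641 = 22.4, total 54.3. Controls supply 22.4/54.3 = 41% of them. A strong determinant of response, arm, is left out of the model.

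**Reading 2: CBT-I arm only.** Expected non-responders are 35 × 0.089 = 3.1, or 26 × 0.089 = 2.3 after attrition (35 × 0.75 ≈ 26), for five named predictors. With no control data, prognosis and benefit over control cannot be separated at any sample size.

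**Simulation.** Change = 8.1 + 5.7 × arm + 5.8 × (r × x + √(1 − r²) × e), with x and e standard normal and response defined as change ≥ 6. The correlation r between predictor and change may differ by arm. All values of r are assumptions, because the documents give none. Entries are the approximate percentage of trials with p < 0.05, at 26 / 35 per arm. With 800 trials the Monte Carlo standard error is at most √(0.25/800) = 1.8 points.

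| r in CBT-I / control | Pooled logistic, predictor only | Logistic, arm-by-predictor | Linear on ISI change, arm-by-predictor |
|---|---|---|---|
| 0.4 / 0.4 (same mean benefit for all) | 42 / 56 | not tabulated | about 5 |
| 0.5 / 0 | 11 / 13 | 8 / 13 | 43 / 56 |
| +0.4 / −0.4 | 10 / 13 | 27 / 41 | 83 / 93 |

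- In a CBT-I-only fit, the purely prognostic factor of the first row is flagged in only about 4% to 12% of trials, because there are so few non-responders.
- Adding an arm main effect to the pooled logistic model without the interaction changes little: 45 / 61, 9 / 13 and 10 / 14 for the three rows.
- Some logistic interaction fits fail through separation, so that column is approximate.

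**The case against.** The strongest reply is that Aim 3 asks a prognostic question and the model matches it. The section title and hypothesis concern who improves, and the phrase "plausible predictors of responders and non-responders to CBT-I" most naturally means people who do or do not respond when given CBT-I. This stands. A reader might infer that the model is wrong for its own hypothesis, or that section 2.5 claims differential benefit. The text supports neither, and a significant prognostic factor is a correct result for a prognostic aim.

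Second, adherence is defined only for CBT-I, so a CBT-I-only fit is plausible. An arm term would then be inapplicable rather than omitted, and the pooled figures would not apply. This also stands, so those figures are conditional on pooling. It does not rescue the stated use, because that reading has no comparator.

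Third, a reader might attribute the whole gap between the pooled model and the linear interaction to the missing interaction. The table does not support that. With correlations 0.5 / 0, a logistic interaction (8 / 13) does no better than the pooled main effect (11 / 13), and the gain to 43 / 56 comes with the continuous outcome. With opposite slopes the interaction itself helps (27 / 41 against 10 / 13), and the continuous outcome adds the rest.

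Fourth, the aim is exploratory, the predictor list is open-ended, and an unseen analysis plan may add terms. The exploratory label excuses low power, but not a stated use that the described model does not address. Nothing in the hypothesis points to an interaction.

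**Conclusion.** The point holds as a mismatch between analysis and stated use. Section 3.2.3 can identify characteristics associated with improvement. On neither reading of the analysis set can it show who gains more from CBT-I than from control, so the individual-selection statements in the Introduction and Discussion do not follow from it.

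That conclusion is structural and needs no numerical assumption. The sizes do. The responder rates rest on the plan's pilot-based ISI figures and normality; the flagging rates rest also on assumed correlations and, for the 42% to 56%, on pooling.

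Severity is modest. Aim 3 is exploratory, the wording is that results help guide a choice rather than determine it, and no primary or secondary efficacy analysis depends on it.

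**What to change.** 1. State in section 3.2.3 which arms enter the Aim 3 analysis.
2. If the individual-selection purpose is kept, use both arms. For each baseline predictor in turn, model the 6-week ISI score on screening ISI, arm, predictor and arm-by-predictor. Report the interaction with its 95% confidence interval, labelled exploratory, and label predictor main effects prognostic. Leave adherence out of these models: it arises after randomisation and is defined only for CBT-I.
3. The responder logistic regression may stay as a prognostic analysis. The interaction should be on the continuous score, because on the binary outcome it has little power (table above).
4. Otherwise, limit the stated use in the Introduction and Discussion to prognosis.

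The cost is some wording and a few model terms, with no new data or participants. The downside is that interaction estimates at 26 to 35 per arm will be imprecise and can only generate hypotheses.
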